#### 2.8.4. Exploratory Data Analysis

Overall change from baseline to 12 and 24 months, categorised as improved, stable, and deteriorated, will be carried out at the following clinical assessments: (i) MRI (brain); (ii) Abdominal ultrasound; (iii) Nerve conduction studies and electromyography; and (iv) Neuro ophthalmological assessment. In addition, changes from baseline in serum or plasma biomarkers related to mitochondrial health such as FGF 21, GDF15, and other markers of mitochondrial condition at Days 0, 1, 7, 14, 21, 28, 35, 42, 43, 49, 56, 63, 64, 70, and 77, and at each clinic visit from Day 78 until the end of the study, will be recorded. Associations between pharmacodynamics parameters and clinical activity parameters will be explored.

#### 2.8.5. Interim Analysis

An interim review of data will be conducted after each of the twelve-adult treatment naïve patients has been exposed to EE-TP for at least one year. This interim time point has been chosen to assess and confirm the potential utility of EE-TP in this population, and to provide potential early access of EE-TP in this population. The exposure for a patient at the interim stage could exceed one year if a patient is recruited early on into the study.

### 2.9. Data Monitoring Committee

The appointed Independent Data Monitoring Committee will oversee safety throughout the trial period. The committee will comprise a chairperson, a specialist in MNGIE, and a statistician. The purpose of the committee will be to review unblinded study information including protocol violations, patient withdrawals, adverse/serious adverse events, and laboratory data. An assessment will be made by the Independent Data Monitoring Committee with regard to the enrolment of juvenile patients.

### 2.10. Patient Confidentiality

Patient confidentiality will be held by the participating investigators and all personnel involved at the study sites. Following Good Clinical Practice principles, a patient number will be used to identify the patient in the study records. Laboratory samples and any samples in storage will be labelled using only the patient number, and the identity of the patient will be known only by the study site. The numbering code associated with the labels will be held by the study sites, thereby allowing no unwarranted access to the information. When reporting results for any interim safety information, analyses, and end of the study, the code will be shared as per sponsor standard operating procedures. The numbering code will also be held for any samples in storage until marketing approval in the countries where the study is conducted, or until notification is received that storage is no longer required.

### 2.11. Dissemination

The results of this study will be disseminated through presentation at international scientific conferences and reported in peer-reviewed scientific journals. We also intend to disseminate our results to the rare disease community.

### 2.12. Ethical Conduct and Approval and Trial Registration

This study will be conducted in accordance with consensus ethics principles derived from the Declaration of Helsinki. Approval for the operation of the clinical trial at the United Kingdom study site was granted following Research Ethics Committee review (18/SW/0266) and Health Research Authority (HRA) and Health and Care Research Wales (HCRW) review. For the non-United Kingdom trial sites, the study will be considered by the relevant Ethics Committee (EC) of each participating country site.

### 2.13. Trial Registration and Status

The trial is registered at ClinicalTrials.gov, with identifier number NCT03866954. The trial is in preparation and is not yet open for participant recruitment.

## 3. Discussion

Mitochondrial neurogastrointestinal encephalomyopathy is a relentlessly progressive disorder with an invariably fatal outcome, and therefore an early diagnosis and subsequent normalisation of deoxynucleosides is critical to avoid ongoing mitochondrial damage and disease progression. The compassionate treatment of patients with regular infusions of EE-TP demonstrated a reduction or elimination of plasma deoxynucleosides and clinical improvements in patients who received long-term treatment, suggesting that EE-TP is able to reverse some aspects of the disease pathology [18,19]. This study aims to determine the safety, tolerability, pharmacodynamics, and efficacy of multiple doses of EE-TP in patients with MNGIE. In practice, treatment with EE-TP is likely to be sought for patients in whom the risk of mortality from allogeneic HSCT would be too high, and also for those for whom there is no matched donor. Treatment with EE-TP may also be indicated as a rescue or maintenance therapy prior to the availability of a suitable HSCT donor, and for patients who are oligosymptomatic and reluctant to undergo HSCT.

The total sample size of 12 adult treatment naïve patients is not based on a formal statistical calculation; it is a relatively small sample size, but this is expected to be offset by the nature of the condition. MNGIE has a predictable clinical course; it is relentlessly progressive, with a very poor prognosis for life, and it has been reported that the mean age of death is 37.6 years (range 15–54 years) [21]. Therefore, any arrest or improvement of patients’ clinical deficits and/or reduction in mortality should be conspicuous and would not be plausibly explained by factors other than treatment with EE-TP. Clearly, such findings would be highly clinically relevant.

The rationale for the dose selection is based on data generated from patients who received EE-TP on a compassionate treatment basis. This indicated that the optimal parameters required to achieve metabolic depletion of thymidine and deoxyuridine were a maximum of 90 U TP/10^10^ erythrocytes and a minimum 58 × 10^10^ erythrocytes. We therefore propose the infusion of an optimum number of ~58–65 × 10^10^ erythrocytes at three dose levels: 30–49, 50–69 and 70–90 U/10^10^ erythrocytes. The starting dose for all patients will be Dose Level 1; this will be administered for at least two treatment cycles (three weeks apart). This initial three week period has been designed to ensure metabolic correction is captured appropriately, and dosing changes can be made accordingly. If metabolic correction is observed, the patient will continue to receive this same low dose. However, if no metabolic correction is observed then the patient will receive Dose Level 2 (mid dose level) for two consecutive treatment cycles. If metabolic correction is still not achieved, treatment will advance to Dose Level 3 (high dose) for subsequent treatment cycles. Both dose and dosing regimens will be flexible.

The study will be open label with a three month run-in period, which is appropriate, as the primary objective is to evaluate the safety, tolerability, efficacy, and pharmacodynamics of EE-TP in patients with MNGIE. Currently, it is not known how variable or what change, if any, in the clinical and metabolic parameters will be observed over this three month run-in period, but these data will primarily serve to act as each patient’s own pre-treatment/control observations. Patients with MNGIE present with a wide variety of clinical (gastrointestinal and neurological) features and these data are highly likely be very heterogeneous between patients. Nonetheless, prolonged treatment with EE-TP is expected to cause positive changes in these various clinical and metabolic endpoints. The decision not to include a placebo control group was taken due to the serious and life-threatening nature of the disease and the evidence available from compassionate treatment data for EE-TP to mediate metabolic correction of thymidine and deoxyuridine levels in patients with MNGIE. Based upon pre-clinical data and compassionate treatment data, the 24 month duration of the study is considered sufficient to assess the safety and tolerability, and to establish the pharmacodynamic effects of EE-TP. There is very limited natural history data available for MNGIE, and no clinical study data to determine the duration of treatment required to detect potential treatment effects. An interim review of open label data will be conducted after each of the 12 adult treatment naïve patients have been exposed to EE-TP for at least one year.

The rationale for the pharmacodynamic objective is based on the biochemical hallmark of MNGIE, where the deoxynucleosides thymidine and deoxyuridine accumulate in the plasma as a result of the deficient thymidine phosphorylase. The accumulation of thymidine impacts deoxynucleoside and nucleotide pools, and is thought to impede mtDNA replication and/or repair leading to mtDNA abnormalities and ultimately, mitochondrial dysfunction. Erythrocyte encapsulated TP is designed to replace thymidine phosphorylase in a sustained manner to reduce or eliminate elevated plasma thymidine and deoxyuridine concentrations. Pre-clinical studies have shown that thymidine and deoxyuridine diffuse across the erythrocyte membrane into the cell, where the encapsulated enzyme catalyses its metabolism to the normal products (thymine and uracil). This should result in a withdrawal of thymidine and deoxyuridine from the cellular compartments, and an amelioration of the intra mitochondrial deoxyribonucleotide imbalances. We hypothesise that by preventing further damage to mtDNA, mitochondrial turnover should allow mitochondrial regeneration, and thus the restoration of mitochondrial function [22]. As an exploratory objective, this study will also assess markers of mitochondrial condition, e.g., FGF21, GDF15, including mtDNA, mRNA, miRNA, and lipidomics/proteomics, and the potential effects of reducing thymidine and deoxyuridine levels on these markers. The pharmacodynamic and clinical data from the retrospective HSCT study supports the hypothesis that biochemical improvement results in clinical improvement, particularly in BMI, and supports the use of pharmacodynamic data as a biomarker for clinical efficacy [13].

Due to the absence of previous data on outcome measures in MNGIE, validated secondary outcome measures, including a quality of life measure, have been selected on the basis of clinical trials in similar disorders. We have chosen not to composite outcome measures due to the marked phenotypic variability of the disorder. No validated composite outcome measure exists for MNGIE. Using assessment/rating scales for mitochondrial disorders more generally (e.g., the Newcastle Mitochondrial Disease Assessment Scale) would be a risk in a very small population, with composite outcomes showing no effect overall, while a more critical individual measure (e.g., BMI, or mortality), would show evidence of benefit [23].

There are generally no accepted endpoints for clinical studies in patients with MNGIE. This ultra-rare disease usually presents with a combination of cachexia, gastrointestinal dysfunction, and neuromuscular dysfunction. Although weight loss is one of the key features of MNGIE and has a major impact on functional status, individual weight loss trajectories are not typically available in published case series. Weight loss is clearly associated with increased morbidity and mortality, and a decreased quality of life in other chronic diseases for which weight loss is a primary manifestation, including cancer [24], chronic obstructive pulmonary disease [25], chronic heart disease [26], chronic kidney disease [27], and acquired immunodeficiency syndrome [28]. Overall, current evidence shows that weight loss is a valid prognostic marker and is associated with decreased quality of life across different conditions. Additionally, at least in patients with cancer, weight loss and symptoms associated with anorexia cachexia have been shown to have a psychosocial effect, not only on patients, but also on the caregivers and families of those affected [29].

Weight is an objective measurement, which is readily obtained without causing additional burden to patients. Objectiveness is a critical requirement within the context of the planned open label design of this study. Serial measurements of body weight offer the simplest screen for nutritional adequacy and change in nutritional status. The weight and height of a patient are used to formulate the BMI (i.e., calculated by an individual’s body mass divided by the square of his/her height (kg/m^2^)). Since weight loss is essentially a universal feature of MNGIE, any weight gain is highly likely to represent a very sensitive clinical objective. Consequently, the primary clinical endpoint in this study will be mean absolute change from baseline in BMI.

Most published case series show a mean BMI of approximately 14 kg/m^2^ in patients with MNGIE, e.g., reference [4] describes 35 patients of which 16 were living at the time. The average height and weight for males were 170 cm and 40.3 kg, respectively, whilst for females were 159.1 cm and 35.5 kg. In the weight range reported for patients with MNGIE, an increase in BMI of approximately 0.2 represents an increase in body weight of approximately 0.5 kg. This increase is well above the measurement error for medical grade scales and is likely to be above intra individual variation for human weights in the low range. Therefore, an increase in BMI of 0.2 kg/m^2^ will empirically be used as a minimum threshold in counting patients with weight increase. Owing to the extreme rarity of the occurrence of MNGIE, a stabilisation of ±0.2 kg/m^2^ in BMI will be deemed to be clinically significant, rather than statistically significant, since it is expected to halt further clinical deterioration. Weight loss is clearly associated with increased morbidity and mortality in a variety of other chronic conditions. If adult patients with MNGIE were able to maintain or slightly increase their BMI with long-term therapy with EE-TP, this stabilisation would highly likely manifest itself in decreased overall morbidity and mortality, and hence overall clinical benefit in this population.

There is limited precedent for weight measurement following intervention for patients with MNGIE. In a retrospective international study of 24 patients with MNGIE treated with HSCT, 7 patients survived more than two years after HSCT, and all gained weight (median weight increase was 2.5 kg at a median follow-up of 53 months) [13]. This weight gain occurred in parallel with increase in TP activity to normal levels and normalisation of thymidine and deoxyuridine levels. Due to the retrospective international nature of the study, no consistent formal clinical outcome measures were documented. Subjective evaluation of clinical examination in two year survivors suggested improvements in muscle strength and sensation, although this was not quantified. A patient who received orthotopic liver transplantation for MNGIE was reported to have cachexia and body mass/BMI monitored, although no improvement was noted [30].

Treatments targeting anorexia and cachexia in other disorders, such as oxandrolone, dronabinol, megestrol acetate, growth hormone, and anamorelin, have previously used weight gain, with lean body mass and handgrip strength being used more recently. The mechanism of action of those products, targeting appetite and hormonal control of food intake, suggests that they would not be effective in patients with MNGIE.

Likewise, there is no systematic information on the illness experience of patients with MNGIE, and no disease specific instrument to collect it. The disease is a multi-system organ disorder with a heterogeneous presentation. Secondary outcome measures have been selected to assess gastrointestinal and peripheral sensorimotor polyneuropathy symptoms. The selected instruments are not disease specific, but have been shown to correlate significantly with both generic and disease targeted legacy instruments, and demonstrate evidence of reliability [31]. In addition, patient global impression of improvement, as well as improvement of the most disabling symptom for each patient, will be assessed.

The precise mechanism through which correction of the enzymatic defect through EE-TP therapy can decrease the elevated circulating levels of thymidine and deoxyuridine, ultimately restoring gastrointestinal function leading to an increase and stabilisation in body weight and improved outcomes, is speculative at this point. Previous research has shown that severe depletion of mtDNA is the main molecular defect in the gut wall of patients with MNGIE [21,32]. The depletion of mtDNA correlates with histopathological abnormalities and is likely due to toxic levels of thymidine and deoxyuridine disrupting the mitochondrial nucleotide pool through an unknown mechanism. The reduction of circulating levels of thymidine and deoxyuridine could, in principle, prevent further mtDNA depletion and, in time, promote the restoration of depleted gastrointestinal smooth muscle mtDNA pools. The consequent potential improvement of intestinal motility and improvement of nutrient absorption can be hypothesised to at least prevent further deterioration of the nutritional status and reduce gastrointestinal symptoms.

In summary, cachexia is the most consistent clinical manifestation of MNGIE. A robust clinical outcome measure of mean absolute change in BMI from baseline at 24 months is the primary endpoint. Stabilisation in BMI over a 24 month period will be regarded as a significant clinical benefit based on the consistent loss in BMI with time in patients with MNGIE. Relevant secondary endpoints included are the proportion of patients who require TPN, handgrip strength (using a dynamometer, according to the Southampton protocol), functional disability assessed by RODS, 10 m walk test, evaluation of gastrointestinal symptoms (PROMIS short form), neurological examination (for the assessment of presentation, improvement, or worsening in motor strength, distal sensory impairment, or areflexia), PGIC, assessment of the most disabling symptom for each patient using VAS, and quality of life. This range of secondary outcome measures will enable capture of clinical effect in a condition for which there is considerable phenotypic variability. 

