## 2. Methods

### 2.1. Trial Objectives

The primary objectives of this study are to determine the safety, tolerability, pharmacodynamics, and efficacy (as measured by weight stabilisation) of multiple doses of EE-TP in patients with MNGIE. The secondary objectives are to assess the immunogenicity of EE-TP after multiple dose administrations, evaluate changes in clinical assessments, and assess the pharmacodynamics effect of EE-TP on clinical assessments. Additional exploratory objectives aim to evaluate the effects of EE-TP on serum and plasma markers of mitochondrial condition, MRI (brain), abdominal ultrasound, electromyography, and neuro-ophthalmological assessments.

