### 2.6. Trial Endpoints

#### 2.6.1. Efficacy Endpoints

The primary efficacy endpoint will be the mean absolute change from baseline in body mass index (BMI) at 24 months. The secondary efficacy endpoints will be the mean absolute change from baseline in BMI at Day 63 and 3, 6, 9, 12, 15, 18, and 21 months, plus the change from baseline at 63 days and 3, 6, 9, 12, 15, 18, 21, and 24 months in: (i) The proportion of patients who require TPN; (ii) Handgrip dynamometry; (iii) RODS; (iv) 10 m walk test; (v) EuroQo-5D; (vi) CGI-I; (vii) PROMIS short form scales; (viii) PGIC; (ix) Neurological examination tests; and (x) VAS for the most disabling symptom.

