### 2.7. Sample Size

The sample size for this study is dictated by the rarity of the condition and not by any quantitative statistical considerations or formal sample size calculations. At least 12 adult treatment naïve patients will be treated in this study, with the option to enrol an additional 8 juvenile patients, beyond this original set of 12 patients.

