### 2.8. Statistical Analyses

Statistical analyses will be primarily descriptive. Analyses will be performed using Statistical Analysis Software^®^ (Version 9.2 or higher, SAS Institute, Cary, NC, USA). For continuous data, summary statistics will include the arithmetic mean, arithmetic standard deviation, median, lower and upper quartiles, plus minimum, maximum, and number. For log normal data, summary statistics, including the geometric mean and geometric coefficient of variation, will also be presented. For categorical data, frequency counts and percentages will be presented. Data listings will be provided for all patients up to the point of withdrawal, with any patients excluded from the relevant population indicated. For the calculation of summary statistics and statistical analysis, unrounded data will be used.

For each study participant the change from baseline will be calculated by subtracting their mean baseline value from the value at the specific time point. The mean change from baseline will be derived as the arithmetic mean of all individual patients’ change from baseline values.

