#### 2.8.3. Efficacy Data Analysis

The changes from baseline for all efficacy endpoints and outcomes will be calculated using data from the run-in period (Day −91 to Day 0) as the baseline. Absolute and percentage changes from baseline in BMI will be plotted. In addition, absolute and percentage changes from baseline in BMI will be recorded against plasma and urine concentrations of thymidine and deoxyuridine. The percentage of patients achieving at least the minimum threshold of weight gain will be presented by dose. Since juvenile patients in the juvenile cohorts will be developing (i.e., growing and maturing) during the study, changes in weight and other efficacy endpoints cannot be reliably attributed to EE-TP, and therefore their data will not be included in the main efficacy analyses, and will be analysed separately.

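### The ±0.2 kg/m² BMI stabilisation criterion is tied to no bound on the loss the data still allow, and the text does not say whether it applies to the mean or to each patient

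*Protocol article*

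**What the plan says.** Section 2.1 gives the primary efficacy objective as "efficacy (as measured by weight stabilisation) of multiple doses of EE-TP in patients with MNGIE". Section 2.6.1 turns this into an endpoint: "The primary efficacy endpoint will be the mean absolute change from baseline in body mass index (BMI) at 24 months".

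The criterion for success appears only in the Discussion. One sentence sets a patient-level count: "an increase in BMI of 0.2 kg/m^2^ will empirically be used as a minimum threshold in counting patients with weight increase". The next says that "a stabilisation of ±0.2 kg/m^2^ in BMI will be deemed to be clinically significant, rather than statistically significant". Two pages of argument later, directly after naming the mean 24-month change as primary endpoint, the summary paragraph adds: "Stabilisation in BMI over a 24 month period will be regarded as a significant clinical benefit".

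Section 2.8 describes the analysis as mainly descriptive, and for continuous data "summary statistics will include the arithmetic mean, arithmetic standard deviation, median, lower and upper quartiles, plus minimum, maximum, and number". No interval is in that list. On numbers, Section 2.7 states "At least 12 adult treatment naïve patients will be treated in this study", with no calculation behind it. For juveniles, Section 2.8.3 says that "their data will not be included in the main efficacy analyses, and will be analysed separately", so the main efficacy analysis rests on about 12 adults.

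**The concern.** To call a group stabilised is to conclude that no important loss has occurred. That conclusion needs a statement of how large a loss the data still permit. The plan attaches a claim of benefit to ±0.2 kg/m² and asks for no such statement.

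The reasons offered for 0.2 are scale error and within-person variation. Neither describes how widely 24-month BMI changes differ between patients, and that spread determines the precision of a mean of 12. Section 2.3 says the variability of the clinical parameters is unknown, and the Discussion expects patients to be very heterogeneous.

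At stake is the main efficacy message of an uncontrolled trial. The Discussion says natural-history data are very limited and that individual weight-loss trajectories are not usually published, so the reader has little outside the trial to set a bare mean against. It also argues that any arrest of decline could hardly be explained by anything but treatment, which puts more weight on the word *stabilised*.

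**Working it through.** **The plan's own figure.** The Discussion equates 0.2 kg/m² with about 0.5 kg. At its mean heights, 0.2 × 1.70² = 0.58 kg for men and 0.2 × 1.591² = 0.51 kg for women. The figure reproduces. The sample size of 12 has no alpha, power or SD behind it, so there is nothing to reproduce.

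**Inputs.** Margin 0.2 kg/m² (Discussion); n = 12 adults (Section 2.7); primary endpoint the mean change at 24 months (Section 2.6.1). The SD of 24-month BMI change is **assumed**, from 0.2 to 2.0 kg/m². The only change benchmark in the document is a median gain of 2.5 kg in seven transplant survivors. At the heights above this is 2.5/1.70² = 0.87 to 2.5/1.591² = 0.99 kg/m². It is not an SD and only gives a sense of scale.

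**Formulas.**
- SE = SD/√12.
- 95% half-width = t(0.975, 11) × SE = 2.201 × SD/3.464 = 0.635 × SD.
- Lower limit at an observed mean of −0.2 = −0.2 − half-width.
- Two-sided reading, true mean loss 0.5: P(−0.2 ≤ mean ≤ 0.2) = Φ(0.7/SE) − Φ(0.3/SE).
- One-sided reading (mean no worse than −0.2): 1 − Φ(0.3/SE). It is shown because the Discussion also speaks of maintaining or slightly raising BMI.

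| Assumed SD | SE | 95% half-width | Lower limit at mean −0.2 | Within ±0.2, true loss 0.5 | No worse than −0.2, true loss 0.5 |
|---|---|---|---|---|---|
| 0.2 | 0.06 | 0.13 | −0.33 | <0.1% | <0.1% |
| 0.3 | 0.09 | 0.19 | −0.39 | <0.1% | <0.1% |
| 0.5 | 0.14 | 0.32 | −0.52 | 2% | 2% |
| 1.0 | 0.29 | 0.64 | −0.84 | 14% | 15% |
| 1.5 | 0.43 | 0.95 | −1.15 | 19% | 24% |
| 2.0 | 0.58 | 1.27 | −1.47 | 19% | 30% |

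**Where the margin is overtaken.** The half-width exceeds 0.2 once SD > 0.2/0.635 = 0.315 kg/m². In weight that is 0.315 × 1.591² = 0.80 kg to 0.315 × 1.70² = 0.91 kg over two years. The SE alone exceeds 0.2 only above SD = 0.2 × 3.464 = 0.69.

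**Could the lower limit simply be required to clear −0.2?** With no true change, the chance that it does is P(T > 2.201), where T is noncentral t with 11 df and noncentrality 0.2 × 3.464/SD. This gives 88% at SD 0.2, 24% at SD 0.5 and 9% at SD 1.0. Except at a very small SD, 12 adults would rarely meet that rule.

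**Mean or patient?** The sentence just before the criterion counts patients. Sections 2.1 and 2.6.1 and the Discussion's summary tie stabilisation to the mean endpoint. The only patient-level analysis in Section 2.8.3 counts patients reaching the minimum weight *gain*, and the article describes no count of patients within ±0.2. The mean is the better-supported reading, but the text does not settle it.

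**The case against.** The strongest reply is that the article claims nothing inferential. The analysis is declared mainly descriptive, the sample size is openly a matter of rarity, and disclaiming statistical significance is candid. A list of statistics that will be included does not exclude others, and confidence intervals are often left to the analysis plan, which is not shown. This stands to the extent that the missing interval alone would not be a finding. The finding is that the text states a criterion for benefit with no precision requirement; an interval added elsewhere would not change that criterion.

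Second, the mean, SD and n will be reported, with quartiles, range, listings and plots of BMI change. A reader might infer that wide opposing changes averaging to zero would go unseen. They would not, and the t-interval can be worked out from the reported figures. What remains is that the stated conclusion does not depend on them.

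Third, ±0.2 may be meant for each patient. On that reading the calculations for a mean do not apply directly. The criterion would then be incomplete in another way, because no proportion of patients is named as amounting to stabilisation.

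Fourth, a reader might infer that sampling error swamps the margin for any plausible SD. The documents do not support this. They give no SD, their remark on heterogeneity is qualitative and not specific to BMI change, and below an SD of about 0.315 the half-width is smaller than the margin.

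**Conclusion.** The concern holds in a limited form. The Discussion will regard BMI stabilisation of ±0.2 kg/m² as a clinical benefit without relating it to any bound on the loss still compatible with the data, and without saying at which level it is judged.

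If it is judged on the mean of 12 adults, an observed −0.2 meets the criterion while leaving a mean loss of up to 0.52 kg/m² (SD 0.5) or 0.84 kg/m² (SD 1.0) unexcluded. A reader might go further and infer that a trial with real loss would probably be declared stable. The figures do not show that: at a true mean loss of 0.5, the chance is about 2% to 19% on the two-sided reading and 2% to 30% on the one-sided reading, for SDs from 0.5 to 2.0.

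All these sizes rest on assumed SDs, on approximate normality of the mean and on 12 adults with a 24-month value. Section 2.7 says at least 12, so the number could be larger; withdrawals without substitution could make it smaller.

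**What to change.** - **Section 2.8.3:** report the adult mean 24-month BMI change with its two-sided 95% t-interval.
- **Discussion, where ±0.2 is introduced:** state that it is judged on the mean. If it is meant for patients, report the proportion within or above it with an exact 95% interval.
- **Discussion, there and in the summary paragraph:** word any stabilisation conclusion from the lower limit, for example *mean change X; mean loss up to Y not excluded*, and not from the point estimate alone.

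Do not make clearing −0.2 a condition, since 12 adults would seldom meet it even with no true change. The statement that no claim of statistical significance is made need not be removed.

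The cost is one more summary statistic and a few sentences, with no added patients or visits. The downside is that a mean near zero will often have to be reported as inconclusive.
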